## Abstract

**Background:**

Paucity and low evidence-level data on proton therapy (PT) represent one of the main issues for the establishment of solid indications in the PT setting. Aim of the present registry, the *POWER* registry, is to provide a tool for systematic, prospective, harmonized, and multidimensional high-quality data collection to promote knowledge in the field of PT with a particular focus on the use of hypofractionation.

**Methods:**

All patients with any type of oncologic disease (benign and malignant disease) eligible for PT at the European Institute of Oncology (IEO), Milan, Italy, will be included in the present registry. Three levels of data collection will be implemented: Level (1) clinical research (patients outcome and toxicity, quality of life, and cost/effectiveness analysis); Level (2) radiological and radiobiological research (radiomic and dosiomic analysis, as well as biological modeling); Level (3) biological and translational research (biological biomarkers and genomic data analysis). Endpoints and outcome measures of hypofractionation schedules will be evaluated in terms of either Treatment Efficacy (tumor response rate, time to progression/percentages of survivors/median survival, clinical, biological, and radiological biomarkers changes, identified as surrogate endpoints of cancer survival/response to treatment) and Toxicity. The study protocol has been approved by the IEO Ethical Committee (IEO 1885). Other than patients treated at IEO, additional PT facilities (equipped with Proteus®ONE or Proteus®PLUS technologies by IBA, Ion Beam Applications, Louvain-la-Neuve, Belgium) are planned to join the registry data collection. Moreover, the registry will be also fully integrated into international PT data collection networks.

## Introduction

External beam radiation therapy (EBRT) can be administered using different fractionation schedules. Hypofractionation (dose/fraction > 2.5 Gy) represents the standard of care for many photon-based treatments both for curative and palliative aims. Compared to the standard fractionation schedule (1.8-2 Gy/fraction), hypofractionation has several advantages, such as higher radiobiological efficacy, shorter overall treatment time, and reduction of patients’ logistic discomfort. As for photon-based radiation therapy (RT), the use of hypofractionation is constantly increasing also in the setting of patients treated with proton therapy (PT) [1].

Several studies have demonstrated the feasibility and efficacy of PT administered by hypofractionation.

Therefore, this schedule could be proposed for different histologies of tumors located in different body sites, such as breast [2], lung [3, 4], prostate [5], liver [6], as well as for reirradiation treatments [7]. Despite this, literature data provides mainly data collected as mono-institutional experience or referred to patients enrolled in clinical trials. The paucity of PT data represents one of the main barrier for the establishment of solid indications in the PT setting. As a matter of fact, in addition to the relative scarcity of data, most of them are collected in a non-standardized or fragmented manner.

Therefore, the aim of the present registry, the *POWER* registry, is to prospectively and systematically collect data on patients treated with PT in order to add on the existing knowledge of suitable indications, feasibility, and clinical outcomes of PT. Moreover, different hypofractionated schedules will be collected in order to compare toxicity profiles and clinical outcomes of the two regimes.

## Methods/design

### Participant eligibility criteria

All patients with any type of oncologic disease (benign and malignant disease) who will be eligible for PT (according to international, national and institutional recommendations) and able to provide informed consent (themselves, or through a designated legal guardian) will be included in the present registry. All tumor histologies located in any sites in the body will be considered. No limitation regarding the treatment approach (surgery and/or systemic treatments) will be applied. This wide-range approach takes into account that (1) indications to protons are continuously evolving thanks to the growing literature evidence (2) as the power registry will collect data from different centers, indications to PT could be different among facilities located in different European Countries (3) the power registry allows to collect data from patients enrolled in different clinical trials (if permitted) which could have specific inclusion criteria. Excluded subjects will be pediatric patients (< 18 years old) and patients with mental disorders or impediments of any kind of nature that may prevent proper understanding of informed consent.

Potential registry participants will be recruited during regular clinical activities, multidisciplinary meetings, and outpatient or inpatient visits at all participating centers, or through referral from other centers. Patients enrolled in clinical trials will also be included.

Subject registration procedures will start concomitantly with the beginning of the clinical activity of the IEO Proton Therapy Facility planned for November 2023. Data collection will continue until the end of the follow-up period. The collection is planned for a full 5-year duration. Follow-up will proceed for at least 2 additional years and analyses will be conducted for further 3 years. Therefore, the project has a planned minimum length of 10 years (5 years of data collection, 2 years of follow-up of the last enrolled patient, and a further 3 years of analysis).

### Treatment characteristics

Participants will be treated with the IBA (Ion Beam Applications, Louvain-la-Neuve, Belgium) Proteus®ONE and/or Proteus®PLUS systems according to the best clinical practice following national and international guidelines.

### Registry design

The *POWER* registry will be a prospective data collection repository managed at the European Institute of Oncology (IEO IRCSS, Milan, Italy). Additional Proteus®ONE Centers in Europe may participate in the present registry. After two years, the registry may be extended to other facilities equipped with IBA products other than Proteous®One machine (e.g. Proteus®PLUS Centers). Any protocol modifications (e.g. changes to eligibility criteria or participating centres) will be communicated through published protocol amendments.

The Governance with additional PT facilities will be defined according to scientific collaboration agreements that will be signed between IEO and participating centers.

In the platform, pseudoanonymized data will be collected and stored respecting all the privacy and security criteria, to prevent data leaks. Data integrity, i.e. the overall accuracy, completeness, and consistency of data, as well as safety in regard to regulatory compliance (e.g. General Data Protection Regulation (GDPR) compliance)) [8] and security, will be maintained by carefully defined processes, rules, and standards. Among all the different institutions, e-mail addresses and regular web meetings will be the main communication channels to share updates, issues, and ongoing results.

The platform will integrate both already available and newly implemented data repositories and will be fully integrated with the already existing IEO infrastructure. In this multifunctional platform collected data will include:

Clinical data
patients’ medical history and comorbidities;Quality of life (QoL) assessed with validated international questionnaires, as well as social behavior and psychological distress data with the collaboration of dedicated specialists, will be collected at baseline and subsequently defined timepoints;acute and late toxicity events, collected according to internationally-validated scales, to identify the toxicity profile of PT;costs borne by patients and institutions, logistic issue and information about patients’ discomfort for cost/effectiveness analyses based on real-world data.
Questionnaires collecting data on patients’ quality of life, as well as toxicity scales, will be defined according to the patients, tumor, and treatment characteristics.Imaging data: computed tomography (CT), ultrasound (US), magnetic resonance imaging (MRI), and positron emission tomography (PET) at baseline and at defined time points (simulation, in-room set-up verification during the treatment, follow-up) will be collected.Dosimetric data:
Dose-volume histogram (DVH) extracted parameters;Constraints used for the optimization process.
Biological data:
tissue specimens, including diagnostic cytologic and pathological specimens (at baseline);patients’ blood and saliva samples (for cancers of the head and neck district) at baseline and defined time points.

Biological samples will be obtained for diagnostic purposes with standardized procedures and will remain stored in the pathological laboratory of each Institution. In the case of the exchange of samples among the participant centers, each step will be defined according to specific agreements between Institutions; samples will be accessible only to the authorized personnel and once the registry is ended they will be disposed of according to Institutional regulations.

All the data will be collected in a REDCap® (Research Electronic Data Capture) database. REDCap is a secure web platform for building and managing online databases and streamlining processes offering a vast array of tools that can be tailored to virtually any data collection strategy. Moreover, REDCap software has an intuitive user interface, improves data entry through real-time validation rules (e.g. automated data type and range check), and provides easy data manipulation and export to common statistical packages (SPSS, SAS, Stata, R/S-Plus). Figure 1 provides a schematic representation of data collected in the proton registry platform.

**Fig. 1 Fig1:**
[figure not shown]
A schematic representation of data collected in the platform

### Registry endpoints

The primary aim of the *POWER* registry is to provide a tool for systematic, prospective, harmonized, and multidimensional high-quality data collection to promote knowledge in the field of PT and investigate the use of hypofractionation in PT.

Moreover, data collected in the present registry will be available to support several research fields such as clinical, psychological, cost/effectiveness, radiologic, and pathological studies.

Endpoints and outcome measures will be evaluated in terms of treatment efficacy (primary outcomes) and treatment toxicity (secondary outcomes):

Primary outcomes:
tumor response rate according to Response Evaluation Criteria in Solid Tumours (RECIST) criteria [9]; other than RECIST, different response evaluation criteria could be used for specific tumors (for example, RANO criteria for tumors of the central nervous system [10]) or in specific clinical settings (for example immune-related immune-responses RECIST (irRECIST)criteria for tumor treated with immunotherapy [11]).the percentage of tumor recurrence assessed by Progression Free survival (PFS) rate;3) rate of death assessed by overall survival (OS);
Secondary outcomes:
incidence of acute and late toxicity according to Common Terminology Criteria Adverse Events (CTCAE V 5.0) [12];patients’ quality of life assessed by internationally validated European Organization for Research and Treatment of Cancer (EORTC) questionnaires;patients’ pain assessed by Visual Analogue Score;patients’ quality of life assessed by Quality Adjusted Life Years (QALYs).

Moreover, cost-effectiveness analysis will be carried out by dedicated questionnaires administered to all patients enrolled in the proton registry study.

These objectives will be developed at three different levels as reported in the following details:

### Level 1: clinical research

Clinical data concerning epidemiology, patients’ social status, habits, comorbidity, medical history, treatment characteristics, outcome, and toxicity will be collected for all enrolled patients. These data will be used for different lines of research:

1.1*Outcomes and toxicity*: clinical data will be collected in order to evaluate clinical outcomes and toxicities.1.2*Quality of life*: patients’ quality of life, as well as analysis of ethical, social, and psychological parameters (collected through collaboration with dedicated specialists), will be collected. Collected data will be used to investigate the impact of new treatment approaches on both patients’ and caregivers’ perception according to different parameters such as age, geographical areas, social and familiar environments. Moreover, differences between patients treated with PT and those treated with standard photon-based approach will be collected, analyzed, and reported.1.3*Cost/effectiveness analysis*: the cost/benefit ratio of PT administered with different fractionation schedules will be analyzed using different parameters such as the patient’s discomfort and quality of life, logistic issues, and national health system costs. Standardized parameters (e.g. QALYs) will be used to report the obtained results and to compare different approaches.

### Level 2: Radiological and radiobiological research

Radiologic images related to CT, US, MRI, and PET will be collected for all patients at baseline and during the follow-up period according to the daily clinical practice. Moreover, simulation CT, as well as all radiologic images acquired during the radiation treatment, will be collected and analyzed for scientific purposes. In detail, different fields of interest will be developed:

2.1*Radiomic analysis*: quantitative data retrieved from both radiologic images and PT treatment plans will be analyzed in order to explore radiomic and dosiomic features for the development of new predictive and/or prognostic models.2.2*Dosiomic analysis*: dosiomic analysis retrieved from dose distribution calculated by the treatment plans will be analyzed in order to develop prognostic and predictive models of both clinical outcomes and toxicity.2.3*Radiobiological modeling*: clinical, radiological, and dosimetric data will be integrated in biological models in order to both validate already published and implement new biological parameters. In particular, Normal tissue complication probability (NTCP) models and Tumor control probability (TCP) models will be used to define toxicity parameters and outcomes endpoint, respectively. The impact of such models according to the different fractionation schedules (hypofractionation vs. standard fractionation) will be analyzed.

### Level 3: Biological and translational research

Biological samples such as cytologic and pathological specimens, blood samples and saliva will be prospectively collected, if not yet available for oncologic procedures, to explore new biological parameters. In particular:

3.1*Biological biomarkers*: different biological samples will be used for both external validation of already existing biomarkers and identification of new ones will be one of the objectives of the present tumor registry. Specific protocols for sample collection, storage, and analysis will be implemented according to tumor sites, histology, and treatment schedule.3.2*Genomic data analysis*: identification of genetic patterns of radiosensitivity and/or radioresistance will be explored on different biological samples. In particular, radiosensitivity index (RSI) [13] will be investigated aiming to achieve a genomic-adjusted radiation dose (GARD) model [14] to be used in clinical practice.

Results of patients treated with PT will be presented as a prospective data collection. Moreover, when possible, results will be compared with: (1) literature data related to comparable cohorts of patients treated with proton- and photon-based approaches; (2) retrospective analysis of comparable cohorts of patients treated with photons at the involved institutions. All the analyses will be supported by the use of advanced statistical analysis.

### Statistical power consideration

Given that this study is a registry and not a study design with a formal hypothesis to be tested, sample size considerations were carried out with a view to exploratory analyses of toxicity as main endpoint in case of hypofractionated regimen.

Limited scientific evidence is currently available regarding the comparison between hypofractionated and standard fractionation schedules in patients treated with protons. Therefore, in order to provide a tentative estimation of sample size for the current registry, results provided by studies performed with photon-based techniques have been considered. Breast and prostate cancer studies have been chosen because both had a large number of analyzed patients and a wide use of hypofractionated schedules in daily clinical practice [15, 16]. Given data published by Whelan et al. [15] regarding toxicity after hypofractionated regimen at 5 years, a sample size of 562 produces a two-sided 95% confidence interval from 1.5 to 4.5% for a proportion of late toxicity of 3%. Given the data from Aluwini et al. [16], regarding toxicity after hypofractionated regimen and frequency at day ≥ 16 urination/voiding, a sample size of 689 produces a two-sided 95% confidence interval from 9.5 to 14.5% when the sample proportion is 12%. If we consider as main endpoint acute toxicity, given the results found in Aluwini et al. [17], a sample size of 1024 produces a two-sided 95% confidence interval from 18 to 23% for a proportion of toxicity 20%. An overall sample size of 2000 patients should allow us to estimate with enough precision acute and late toxicity of main cancer sites.

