Compared to the ongoing projects, the present registry will prospectively collect not only clinical data but also radiologic images and dosimetric data obtained from the treatment plan (Level 2 in the present registry) as well as biological samples (translational research Level 3). Moreover, analyses on the impact of PT on patients’ quality of life, and cost-effectiveness studies will be implemented through the collected data. In addition, subanalyses regarding results of hypofractionated schedules in terms of both oncological outcomes and toxicity profile will provide further scientific evidence aiming to implement this approach in daily clinical practice. This latter represents the primary goal of the present data collection due to either the still limited number of facilities actually in operation or the high costs of the PT which represent among the most important limitations for the widespread implementation of this technique in the setting of cancer patients cure.

We are aware that the scientific level I evidence can be achieved mainly by controlled trials. However, real-world data (such as those provided by tumor registries) have been recognized as a valuable tool aiming to help validate findings from clinical trials and confirm (or not) the effectiveness and safety of some treatments [25]. Therefore, the aim of the present registry is to optimize data collection of patients treated with PT in order to provide reliable real-world data on the topic.

Moreover, subgroup analysis will be conducted in order to provide information on homogeneous cohorts of patients and limit the spread of the collected data.

Finally, as the planned length of the project could be not sufficient to address specific issues (like long-term toxicity in surviving patients) an extension of the patients’ enrollment and follow-up will be evaluated.

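### The 1.5 to 4.5% interval for 5-year late toxicity assumes complete 5-year follow-up of 562 patients, but the timeline commits only 2 years for the last enrolled

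*Protocol article*

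**What the plan says.** The Statistical power consideration section of the protocol article sizes the registry for exploratory estimation of toxicity under hypofractionation and calls the result tentative. For late toxicity it borrows a rate from a photon breast study: "regarding toxicity after hypofractionated regimen at 5 years, a sample size of 562 produces a two-sided 95% confidence interval from 1.5 to 4.5" per cent, "for a proportion of late toxicity of 3" per cent. Two parallel statements follow, for 689 and 1024 patients. An overall 2000 is then said to be enough for acute and late toxicity in the main cancer sites.

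The Participant eligibility criteria section gives the timeline: "5 years of data collection, 2 years of follow-up of the last enrolled patient", then three years of analysis. The same section describes the follow-up as a minimum of two further years.

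The Discussion concedes a limit, "as the planned length of the project could be not sufficient to address specific issues (like long-term toxicity in surviving patients"), and says that an extension will be considered. The Registry endpoints section lists the incidence of acute and late toxicity without a time point.

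**The concern.** The sizing sentence and the timeline do not fit together. A binomial interval on a 5-year rate needs the 5-year status of every patient counted in n. Under the committed timeline, a patient enrolled in year 3, 4 or 5 is not followed to 5 years. No allowance for this appears in the sizing.

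At stake is the precision claimed for late toxicity, on which the registry is partly sized. The closing paragraph of the Level 3 section also plans comparison with published proton and photon cohorts. A late-toxicity figure based on 2 to 7 years of follow-up is not comparable with a 5-year figure unless censoring is handled.

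**Working it through.** **1. Reproduce the plan's figure.** Inputs from the Statistical power consideration section: p = 0.03, n = 562, two-sided 95%. The formula that fits is the Wald interval with continuity correction:

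half-width = 1.96 × √(p(1−p)/n) + 1/(2n)

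- At n = 562: 1.41 + 0.09 = 1.50 points, giving 1.5 to 4.5%. The smallest n with a half-width of 1.5 points is exactly 562.
- The same formula returns exactly 689 for 12% ± 2.5 points and exactly 1024 for 20% ± 2.5 points, so the method is identified.
- Plain Wald would need only 497. Clopper-Pearson at 562 gives 1.8 to 4.8%.

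The formula has no term for censoring, death or loss.

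**2. Share of patients followed to 5 years.** Enrolment lasts 5 years and committed follow-up closes 2 years later, so a patient enrolled at time e has 7 − e years. Reaching 5 years requires e ≤ 2. The accrual pattern is not given, so these are assumptions:

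- Uniform accrual: 2/5 = 40% reach 5 years, 60% are censored earlier.
- Ramp over two years, then flat: 25% reach 5 years.
- Linear rise throughout: (2/5)² = 16% reach 5 years, 84% are censored earlier.

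A rise is plausible, because the registry opens at one facility and other centres may join later. Death and loss lower all three shares.

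**3. Precision with a censoring-aware estimate.** For a rare event with constant hazard, the variance of the 5-year estimate is inflated by the average over 0 to 5 years of 1/P(follow-up ≥ t). This probability is 1 up to 2 years. After that it is (7−t)/5 (uniform) or ((7−t)/5)² (linear rise).

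- Uniform: (2 + 5 ln 2.5)/5 = 1.316; effective n = 562/1.316 = 427.
- Linear rise: (2 + 7.5)/5 = 1.90; effective n = 562/1.90 = 296.

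Putting the effective n into the plan's own formula, so that like is compared with like:

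| Accrual | Effective n | Half-width (points) | Interval |
|---|---|---|---|
| Complete follow-up (as printed) | 562 | 1.50 | 1.5 to 4.5% |
| Uniform | 427 | 1.62 + 0.12 = 1.7 | 1.3 to 4.7% |
| Linear rise | 296 | 1.94 + 0.17 = 2.1 | 0.9 to 5.1% |

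A simulation of Kaplan-Meier estimates under uniform accrual agrees. With constant hazard the effective n is about 416 without other loss and 359 with 5% loss per year. With a rising hazard it is 374 and 316.

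**4. Only patients with 5-year status.** Uniform accrual leaves 562 × 0.40 = 225 patients, and the plan's formula gives 0.5 to 5.5%. To have 562 with 5-year status, 562/0.40 = 1405 must be enrolled; under the linear rise, 562/0.16 ≈ 3513.

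**5. Crude proportion over all enrolled, for reference.** With a constant hazard and a true 5-year rate of 3%, the expected crude figure is roughly 3% × mean(min(follow-up, 5))/5.

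- Uniform: 3% × 4.10/5 = 2.5%.
- Linear rise: 3% × 3.56/5 = 2.1%.

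**The case against.** - **The 5 years belong to the cited study.** The registry sets no late-toxicity horizon of its own. This is true, but it does not rescue the figure. If the horizon is 5 years, the precision is overstated; if it is shorter, a 5-year rate is the wrong planning input.
- **No crude proportion is planned.** A reader might infer that late toxicity will be analysed as a crude proportion and so be understated. The document does not support that. The binomial interval is a sizing device, no estimator is named, and the choice may sit in an analysis plan that is not shown. Step 5 applies only if that choice were made.
- **Follow-up is a minimum.** It may run longer, but nothing beyond two years after the last enrolment is committed.
- **The registry plans 2000 patients.** Under uniform accrual 40% of these is 800, more than 562; under the linear rise 16% is 320, fewer. The precision is claimed for the main cancer sites, however, and no split by site or fractionation is given. The shortfall therefore concerns 562 patients in one site and regimen, not necessarily the pooled registry.
- **The limit is disclosed.** The Discussion does name long-term toxicity as an issue that the planned length may not cover. It does not revise the interval.
- **The loss is small.** This stands: with a suitable estimator it is 0.2 to 0.6 points, in a registry that tests no hypothesis.

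**Conclusion.** The point holds in a limited form. As a statement about a 5-year rate, the 1.5 to 4.5% interval does not follow from 562 enrolled patients under the committed timeline. By the plan's own formula the half-width is about 1.7 points (uniform accrual) to 2.1 points (linear rise), against 1.5 stated. Those figures assume a constant hazard, no death, no other loss and closure two years after the last enrolment. The 60% and 84% censored are likewise assumptions about accrual, not figures from the document.

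This is a correction to a stated precision, worth making because it is cheap. It is not evidence of a biased analysis or of an inadequate overall sample size. The much wider interval in step 4 arises only if incompletely followed patients are discarded, which the document does not propose.

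**What to change.** In the Statistical power consideration section, do one of the following:

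1. Restate late-toxicity precision for a 5-year cumulative incidence with death as a competing event (Aalen-Johansen): about 3% ± 1.7 to 2.1 points for 562 enrolled, with the accrual assumption stated and a further allowance for death and loss.
2. Say that 562 means patients with known 5-year status, which needs about 1405 enrolled in that site and regimen under uniform accrual.
3. Base both the rate and the interval on a horizon that planned follow-up covers for all patients, such as 2 years. The 3% must then be replaced by a rate for that horizon.

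Whichever is chosen, report late toxicity as a cumulative incidence at a fixed time with numbers at risk, particularly beside 5-year literature cohorts.

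Options 1 and 3 cost only wording and, for option 1, a slightly less favourable stated precision; enrolment does not change. Option 2 also leaves the total of 2000 as it is, but shows that one site and regimen would take 1405 of it, leaving 595 for everything else.

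### The step from the plan's own precision figures (562, 689 and 1024 hypofractionated patients) to 2000 all-comers for the main cancer sites does not follow, and the third interval is misstated

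*Protocol article*

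**What the plan says.** All of this is in the protocol article.

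- **Purpose of the sizing** (Statistical power consideration). The article says that "this study is a registry and not a study design with a formal hypothesis to be tested" and sizes the registry for "exploratory analyses of toxicity as main endpoint in case of hypofractionated regimen". It calls the estimate tentative.
- **Sources** (same section). The rates come from photon studies: "Breast and prostate cancer studies have been chosen because both had a large number of analyzed patients".
- **Three precision calculations** (same section; the closing figures are percentages). First: "a sample size of 562 produces a two-sided 95% confidence interval from 1.5 to 4.5% for a proportion of late toxicity of 3". Second, for daytime urinary frequency: "a sample size of 689 produces a two-sided 95% confidence interval from 9.5 to 14.5% when the sample proportion is 12". Third, for acute toxicity: "a sample size of 1024 produces a two-sided 95% confidence interval from 18 to 23% for a proportion of toxicity 20".
- **Conclusion** (same section). "An overall sample size of 2000 patients should allow us to estimate with enough precision acute and late toxicity of main cancer sites".
- **Who is enrolled** (Participant eligibility criteria). Benign and malignant disease both qualify, and "All tumor histologies located in any sites in the body will be considered". Level 2, item 2.3, compares hypofractionation with standard fractionation, so the 2000 include both.

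**The concern.** The three calculations count hypofractionated patients for a particular endpoint, while the conclusion counts everyone in the registry and extends to several sites. Nothing printed connects the two. The three intervals are also the only definition of adequate precision in the article, so the concluding sentence has to be judged against them.

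At stake is how site-level toxicity results will be read. The Discussion makes hypofractionation a main goal and promises subgroup analysis in homogeneous cohorts. A reader who trusts the sentence would expect intervals of about ± 1.5 to 2.5 points in each main site. Separately, the third interval is not centred on its own proportion: it lies 2 points below and 3 points above.

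**Working it through.** **Inputs** (Statistical power consideration): n = 562, 689 and 1024; p = 3%, 12% and 20%; total 2000. The number of sites, their mix and the hypofractionated share are not stated, so the values used for them below are assumptions.

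**Step 1. Reproduce the plan's figures.** The Wald half-width with continuity correction is h = 1.96 × √(p(1 − p)/n) + 1/(2n).

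- n = 562, p = 3%: 1.41 + 0.09 = 1.50 points, giving 1.5 to 4.5%. As printed.
- n = 689, p = 12%: 2.43 + 0.07 = 2.50 points, giving 9.5 to 14.5%. As printed.
- n = 1024, p = 20%: 2.45 + 0.05 = 2.50 points, giving 17.5 to 22.5%. Printed as 18 to 23%.

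Solving h = 1.5, 2.5 and 2.5 points for n returns exactly 562, 689 and 1024. The sample sizes are therefore right, and only the third interval is off. Plain Wald would give 497, 650 and 984, so the continuity-corrected form is the one to use for comparison.

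**Step 2. Compare with 2000.**

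- Share of enrolment that one site must supply as hypofractionated cases: 562/2000 = 28.1%; 689/2000 = 34.5%; 1024/2000 = 51.2%.
- Two sites at the acute target: 2 × 1024 = 2048, more than 2000.
- If half of all patients were hypofractionated (assumption), there would be 1000 in total, fewer than the 1024 needed for one site.
- Most favourable reading, with only the two source sites: 562 for breast late toxicity (breast by elimination, since the second endpoint is urinary) plus 1024 for acute toxicity (site not labelled; prostate inferred, in which case it also covers the 689). The sum is 1586, or 79.3% of 2000. That leaves 414 places for every other site and for all standard-fractionation patients.

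**Step 3. Precision under an assumed mix.** Take six equal sites: breast, lung, prostate and liver (Introduction), head and neck (Registry design) and central nervous system (Registry endpoints). The article does not call these the main sites. Half-widths in points, by the formula in Step 1:

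| Assumption | n per site | 3% | 12% | 20% |
|---|---|---|---|---|
| Plan's targets | 562 / 689 / 1024 | 1.5 | 2.5 | 2.5 |
| All hypofractionated | 2000/6 = 333 | 2.0 | 3.6 | 4.4 |
| Half hypofractionated | 1000/6 = 167 | 2.9 | 5.2 | 6.4 |

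Relative to the targets, this is 1.3 to 1.8 times as wide in the first case and 1.9 to 2.5 times in the second.

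**The case against.** The text is hedged. It calls the estimate tentative and the analyses exploratory, tests no hypothesis, and attaches no decision to the 2000. The Discussion also foresees extending enrolment and follow-up. This limits the seriousness, but it does not supply the missing step from the three figures to the total.

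Four stronger readings are tempting, and the article does not support them.

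- *Every site needs 562 to 1024 patients.* The article does not say so. The figures belong to three particular endpoints and rates.
- *2000 cannot work even for breast and prostate.* It can, if 79% of enrolment is hypofractionated disease of those two sites, since 1586 is below 2000.
- *Site-level intervals will be twice as wide as stated.* With six equal sites, that holds roughly if half the patients are hypofractionated. If all are, the factor is 1.3 to 1.8.
- *The 1024 is miscalculated.* It is exact for 20% ± 2.5 points. The printed limits look like 17.5 and 22.5 rounded up. An exact binomial interval (17.6 to 22.6%) would also round to 18 and 23, but the exact method does not give the printed limits for n = 562 (1.8 to 4.8%). The slip is presentational and nothing else depends on it.

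The lack of a stated case mix is not itself a fault in a condensed article, because the full protocol may give one. The fault is that the article draws a conclusion which its printed figures do not carry.

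**Conclusion.** The point holds, at moderate severity. By the plan's own standard, 2000 patients across all sites and both schedules do not give the stated precision for several main sites. For acute toxicity they give it for one site at most, and only if 51% of all enrolled patients are hypofractionated cases of that site. For late toxicity, even an entirely hypofractionated registry fits three sites at n = 562 (2000/562 = 3.6) or two at n = 689 (2000/689 = 2.9). These counts are arithmetic on printed numbers. The widening to 2.0/3.6/4.4 or 2.9/5.2/6.4 points rests on the assumed six equal sites and the assumed hypofractionated share. The 79% figure rests on inferring prostate for the 1024. The third interval should be corrected whatever view is taken of the rest.

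**What to change.** Keep 2000. Replace the last sentence of Statistical power consideration with the precision actually delivered, by the method that reproduces the plan's figures (half-widths in percentage points):

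| Hypofractionated patients | 3% | 12% | 20% |
|---|---|---|---|
| 100 in a site | 3.8 | 6.9 | 8.3 |
| 200 in a site | 2.6 | 4.8 | 5.8 |
| 400 in a site | 1.8 | 3.3 | 4.0 |
| 2000 pooled, if all are hypofractionated | 0.8 | 1.4 | 1.8 |

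At n = 100 and 3% the lower limit falls below zero (3 − 3.8), so use an exact or Wilson interval in that cell; the exact one is 0.6 to 8.5%.

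Then limit the claim to pooled estimates, or to sites that reach the n already printed for the endpoint concerned, and call other site-level estimates descriptive. Change the third interval to 17.5 to 22.5%.

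The cost is one rewritten paragraph and a less favourable statement of precision. No extra patients or design changes are needed.
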